### 2.2. Hospital Group

#### 2.2.1. Cardio-pulmonary Rehabilitation Group Program Conducted in Face-to-Face Format at the Hospital

Due to the current absence of standardized exercise physiology protocols in pediatric cardiology [22], we developed a structured program based on cardio-pulmonary physiology and the limited scientific evidence available up to the present moment [13,23,24]. The sessions were group-based (2–3 patients) and supervised by a pediatric physiotherapist, a pediatric nurse, and a pediatrician specialist in cardiology or a pediatric rehabilitation doctor. Patients were encouraged to maintain their habitual activities during the protocol.

The program will take place twice a week for 12 weeks.

Components of the program:Respiratory Physiotherapy Program: This part of the program incorporates two distinct device-based respiratory training modalities. Our literature review found no previous documentation of respiratory physiotherapy protocols specific to different CHD classifications [13,23,24,25,26] except for patients with Fontan circulation where only techniques with inspiratory muscle training (IMT) devices [27,28,29] or educational sessions with respiratory awareness techniques [30] were used. The objective is to increase inspiratory volume, since most of the patients with CHDs have a restrictive ventilatory pattern (to be determined after ergo-spirometry analysis) and weakness of the respiratory muscles [31]. Children with obstructive or mixed respiratory patterns will also benefit from this program. Improvements in lung inflation have a direct impact on bronchial obstruction.
○Coach 2 volumetric incentive device with 4000 mL (DHD Healhcare^®^ USA (Coach^®^ 2 Incentive Spirometer, 4000 mL, Smiths Medical ASD, Inc., Plymouth, MN, USA)): The patient maintains an upright seated position with proper trunk alignment, with their feet on the floor and holding the device at eye level with both hands. The physiotherapist will ask the patient to exhale slowly until the RV is reached and immediately inhale slowly to perform a maximum inspiration through the mouthpiece, ensuring lip sealing and trying not to block the mouthpiece with the tongue. The piston must be raised as high as possible. At the same time, the children must ensure that the training indicator on the right, indicative of the inhalation speed, floats between both limits. The highest value of the three procedures performed will be recorded as a reference for the intervention. They will perform three sets of ten repetitions with a 5-s apnea to take advantage of collateral ventilation.○Threshold IMT (Threshold IMT, Philips^®^ Respironics, Inc., Murrysville, PA, USA): The objective is to enhance inspiratory muscle strength to increase inspiratory volumes. The resistive load creates negative pressure that helps open the airway and allows better air filling in the lung. The participants will be seated with their feet flat on the floor and an upright trunk. It is important to adjust the mouthpiece by closing the lips tightly around it. A nose clip will be worn to ensure that patients are breathing exclusively through the training device; the child must inhale with enough force to overcome the resistance of the spring and for the valve to open the air passage using diaphragm musculature, trying to expand the rib cage, to avoid the use of accessory muscles; we will progressively tighten the device until the pressure in cmH_2_O is reached, until the child can overcome the maximum resistance at which air can enter his lungs (PIM). This procedure will be performed 3 times, and we will take as reference the highest mark. The maneuvers will be supervised the whole time by an experienced physiotherapist. They will perform three sets of ten repetitions at 30% of the maximum tested in the first month. Once the first month is over, the maximum will be calculated again, and work will be performed at 60% of this value. Once the second month is over, the maximum will be calculated again and work will be performed at 60% of the new value.○Children will take both devices home and perform the same intervention once a day. Duration: 15 min. Each participant kept a diary of usage at home.Aerobic training: Before starting the training, nursing staff will measure O_2_ saturation, blood pressure, and heart rate. Continuous aerobic training is the main component of this group. Patients will undergo the training program with the physiotherapist. The child will work within the heart rate ranges established after performing ergo-spirometry. Moderate intensity exercise will be performed. At the beginning of the training, the child will be working with a heart rate closest to the first ventilatory threshold (VT1). Gradually, based on the monitored child’s tolerance and their perception on the Modified Borg scale (0–10), the heart rate will progressively shift towards the second ventilatory threshold (VT2) [32]. Patients will alternate their training, using a Bike ergometer for pediatric use, Ergoselect 150 (Ergoline^®^ GmbH, Bitz, Germany), or a Treadmill RAM 870 clinical (Medisoft^®^ RAM Italia S.r.l., distributed by MGC Diagnostics Corporation, Saint Paul, MN, USA). Training will be conducted under medical supervision with Telemetry monitoring system ers.2 Software ers.2 (Ergoline^®^ REHAB system ers.2 GmbH, Bitz, Germany) for safety, and this will be perceived by the patient and their families. Patients will be taught to identify symptoms and signs to stop physical exercise both in the hospital setting and in natural environments. These symptoms include chest pain, tightness, palpitations, a significant increase in shortness of breath, dizziness, fainting, unusual fatigue and nausea, signs of paleness or cyanosis in the skin, lips, or nails, or cold or sweaty skin. Warm-up exercises = 5 min, continuous aerobic training = 20 min, cool-down exercises = 5 min.Resistance training: To perform this part of the training, patients will be monitored at all times to ensure safety. Strength-resistance interval aerobic training will be performed. The lower body will be worked more intensively, including the soleus, gastrocnemius, quadriceps, hamstrings, adductors, and gluteus (Bauer pump). Examples: Wide squat, dynamic lunge, high pitch, butt kicks, high knee pointed toe, etc., along with abdominal and diaphragmatic muscles (thoracoabdominal pump/thoracic suction) and standing percussion exercises to activate the plantar venous pump (Lejars venous sole). Examples: Jump high knee pointed toe, etc. All of these exercises enhance venous return and promote preload of the heart, increasing the efficacy of the Frank–Starling mechanism. In addition, they enhance the expanding respiratory muscles of the thoracic cage, mainly the serratus and pectoralis muscles in the closed kinetic chain. Example: From supine 90/90 hip and knee position to oblique sitting synchronized with breathing. The children will begin with 10 s of work and 10 s of rest, and halfway through the training period, that will increase to 20 s of work and 10 s of rest, while maintaining the proposed heart rate ranges for their training at all times. The program will be increased by introducing the step or low-resistance weights, and calisthenics and avoiding at all times intense isometry or Valsalva. All the proposed exercises will be synchronized with breathing. Duration: 15 min.Stretching exercise program: To conclude the program, the physiotherapist will lead stretching exercises, primarily targeting shortened muscles (specific to each patient) and those involved in the training program. Postural-adjusted static and active stretching or active stretching with postural feedback will be performed. Examples: Standing forward fold to hamstring stretch with pelvic lift, prone quad stretch, standing quad stretch with pelvic tilt extension, seated forward stretch with ischial alignment and upright posture, seated wide-leg stretch for adductors and upright posture, seated butterfly stretch and upright posture, dynamic calf and soleus stretch with alternating knee flexion. Duration: 5 min.

Total time for continuous and interval aerobic exercise: 40 min.

Total duration of the complete cardio-pulmonary rehabilitation group: approximately 1 h.

#### 2.2.2. Study Group—Home-Based Cardio-pulmonary Rehabilitation Group

Patients assigned to this group will perform the CRP at their own home. The prescribed physical exercise will be uploaded in video format on the TELEA platform belonging to Galician Health Service (SERGAS). The patients will attend the hospital once at the beginning of the study to learn the program with the physiotherapist, who will tell them what their training heart rate is and the safety ranges in which they should move, and once again at the end of the first month. The program will take place twice a week in their home for 12 weeks. Patients will be encouraged to maintain their habitual activities during the protocol.

Components of the program:Respiratory Physiotherapy Program: Children will use two types of respiratory training with devices—COACH and IMT. The home-based rehabilitation program will follow the same respiratory physiotherapy regimen as the hospital-based group, except for the final phase of incremental resistance in IMT. These children will attend the hospital in person only at the start of and at the end of the first month. They will perform three sets of ten repetitions at 30% of the maximum tested in the first month. Once the first month is over, the maximum will be calculated again, and work will be performed at 60% of this value.
○The intervention will be carried out once a day. Duration: 15 min. Each patient will report the completion of the program through the TELEA platform. TELEA is a remote healthcare platform. This platform enables healthcare professionals to monitor and track the health status of patients in their homes, facilitating communication and reducing the need for hospital or clinic visits. Through TELEA, patients can record their vital signs and other health data, which are monitored in real-time by healthcare professionals. TELEA supports communication via videoconferencing and other digital tools, for instance, the video tutorial of the exercise home program, enhancing accessibility and the quality of healthcare services. Children will carry out the home program following the exercises of the video tutorial (Figure 1).Aerobic interval training: Patients will be monitored during physical exercise with a Heart Rate Monitor with ANT and Bluetooth wireless technology (HRM-Dual™), Garmin Ltd., Olathe, KS, USA. Legally domiciled in Schaffhausen, Switzerland) and GPS running watch Forerunner 45S (GARMIN^®^ Ltd., Olathe, KS, USA. Legally domiciled in Schaffhausen, Switzerland). The child will work within the heart rate ranges established after performing ergo-spirometry. Moderate intensity exercise closest to the first ventilatory threshold (VT1) will be performed. Gradually, based on the monitored child’s tolerance and their perception on the Modified Borg scale (0–10), the heart rate will progressively shift towards the second ventilatory threshold (VT2). They and their families will be taught to identify the symptoms and signs to stop physical exercise, just like the control group. Patients will download their heart rate and Modified Borg scale data after each session and can establish contact through the TELEA platform with the nursing staff of the cardiac rehabilitation unit at all times to resolve any questions they may have. Children in this group will not perform continuous aerobic exercise. They will perform interval aerobic exercise through bodyweight-based strength endurance training, following the same physiological principles explained for the control group. Exercises like wide squat, dynamic lunge, high pitch, jump, butt kicks, etc., will be performed. Some of them are shown in Figure 1 and Figure 2. Duration: 40 min.Stretching Exercise Program and Cool-down Exercises: to conclude the program, stretching exercises will be performed just like the control group. Duration: 5–10 min.Total duration of the complete program: approximately 1 h.(Figure 1 and Figure 2).

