### Main and Secondary Objectives

Main Objectives:To evaluate whether our proposed cardio-pulmonary rehabilitation program improves respiratory function and exercise capacity.To compare outcomes between the hospital-based rehabilitation group and the home-based rehabilitation group.

Secondary Objectives:To identify whether this specific CRP achieves higher adherence rates compared to other programs reported in the literature.To determine if adverse effects occur during or after completing the program.To verify whether the program has been conducted in a safe environment and assess its feasibility in natural settings.To determine if the program leads to improvements in the quality of life of these children and their families.

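### Adverse effects are detected unequally by design in the hospital and home arms, so counts set side by side are likely, though not certain, to favour the home arm

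*Protocol article*

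**What the plan says.** All references are to the protocol article.

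**Objectives.** Main and Secondary Objectives lists two safety aims among the secondary objectives: "To determine if adverse effects occur during or after completing the program" and "To verify whether the program has been conducted in a safe environment and assess its feasibility in natural settings". A main objective is "To compare outcomes between the hospital-based rehabilitation group and the home-based rehabilitation group".

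**Hospital arm (Section 2.2.1).** Sessions are "supervised by a pediatric physiotherapist, a pediatric nurse, and a pediatrician specialist in cardiology or a pediatric rehabilitation doctor". Before training, "nursing staff will measure O_2_ saturation, blood pressure, and heart rate". During aerobic work, "Training will be conducted under medical supervision with Telemetry monitoring system". These children also use the two respiratory devices daily at home, unsupervised, and keep a usage diary.

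**Home arm (Section 2.2.2).** Children attend in person at the start and at the end of month one. They are told their training heart rate and "the safety ranges in which they should move". They exercise with a heart-rate strap and watch, and "Patients will download their heart rate and Modified Borg scale data after each session". They can enter vital signs in TELEA, which professionals are said to follow in real time, and can contact the nursing staff at any time. Child and family learn the same stop symptoms as the hospital arm.

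**Both arms.** Section 3.2 requires serious adverse events to be documented and reported to the principal investigator within 24 h. Section 2.6 gives a general chi-square test for categorical variables and does not mention adverse effects.

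**The concern.** An adverse effect is counted only if it occurs and someone records it. In this trial the second step depends on the arm. A rhythm disturbance without symptoms during a hospital session can show on telemetry, and a pallor that the child ignores can be seen by the physiotherapist. At home the same event is recorded only if it changes the heart-rate trace in a way someone notices, or if the child or family recognises and reports it.

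At stake is the conclusion on safety in natural settings. Section 3 presents home programmes as increasingly favoured, and Section 3.2 already calls the risk from therapy minimal. A low count at home would readily be taken as confirmation, in the arm that is less able to show otherwise. The eligible children include transplant recipients and children with residual haemodynamic defects, so this conclusion matters.

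**Working it through.** **Step 1. Routes of detection side by side.**

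| Route | Hospital arm | Home arm |
|---|---|---|
| Staff watching the session | Yes | No |
| Vital signs before the session | Measured by nurses | Patient may enter them in TELEA |
| Monitoring during exercise | Telemetry under medical supervision | Heart-rate strap and watch, data sent afterwards |
| Symptoms noticed by child or family | Yes, taught | Yes, same teaching |
| Contact with staff | At each of two sessions a week | Two hospital visits, plus TELEA contact |
| Serious-event rule | Yes | Yes |

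The last row and the symptom teaching are common to both arms. The first three rows and the frequency of contact differ because of how the interventions are built.

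**Step 2. The only figure from the plan.** Section 2.4 gives 26 per group. A two-sample t test with d = 0.8, two-sided 5% level and 80% power (noncentral t) needs 25.52, rounded up to 26, so the figure reproduces. It is used below only as the number per arm.

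**Step 3. Size of the distortion, on assumed rates.** The documents give no adverse-effect rate and no detection probability. Assume:
- p, the true proportion of children with an event, is 0.20 in both arms (range 0.10 to 0.30);
- detection s is 0.90 in hospital and 0.70, 0.50 or 0.30 at home.

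Recorded risk = p × s. Expected recorded children = 26 × p × s. Apparent risk ratio = s(home) / s(hospital).

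- Hospital: 26 × 0.20 × 0.90 = 4.68.
- Home, s = 0.70: 26 × 0.20 × 0.70 = 3.64; ratio 0.70/0.90 = 0.78.
- Home, s = 0.50: 26 × 0.20 × 0.50 = 2.60; ratio 0.50/0.90 = 0.56.
- Home, s = 0.30: 26 × 0.20 × 0.30 = 1.56; ratio 0.30/0.90 = 0.33.

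**Step 4. How often the home arm records fewer events.** Two independent binomial counts with 26 per arm:

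| Home detection | Home fewer, p = 0.20 | Home more, p = 0.20 | Home fewer, p = 0.10 to 0.30 |
|---|---|---|---|
| 0.90 (equal) | 0.43 | 0.43 | 0.40 to 0.44 |
| 0.70 | 0.58 | 0.28 | 0.50 to 0.64 |
| 0.50 | 0.74 | 0.15 | 0.61 to 0.82 |
| 0.30 | 0.88 | 0.05 | 0.73 to 0.94 |

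**Step 5. What could be hidden.** The arms would look alike if the true home risk were s(hospital)/s(home) times the hospital risk: 0.90/0.70 = 1.3, 0.90/0.50 = 1.8 or 0.90/0.30 = 3.0.

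**Step 6. Direction.** If detection were instead 0.70 in hospital and 0.90 at home, the ratio would be 0.90/0.70 = 1.29 and the bias would run the other way. Step 1 makes that the less plausible order, but the documents do not exclude it.

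**The case against.** The strongest reply is that the plan announces no between-arm test of adverse effects. The safety objective asks whether they occur, the section on outcomes covers spirometry, exercise capacity and quality of life, and Section 2.6 names no adverse-effect analysis. This stands: a reader might infer that a biased test is written into the plan, and it is not. The comparison follows from the main objective to compare outcomes between arms and from the plain fact that two-arm results are tabulated side by side. The concern is therefore conditional on such a comparison being made or read.

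Second, the home arm is not unwatched. The strap and watch, TELEA, nursing contact and the common serious-event rule all narrow the gap, and the hospital arm has unsupervised daily device work of its own. This also stands in part. TELEA follows what patients choose to enter, and session data arrive afterwards, so the gap narrows, mainly for serious events, without closing.

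Three stronger readings are tempting and not supported:
- That the home programme will look safer than it is. The size rests on assumed rates, and with 26 per arm chance can reverse the order (probability 0.28 at 70% home detection and 20% risk).
- That falls in saturation during exercise would be seen in hospital and missed at home. Section 2.2.1 documents saturation only before training and does not say that telemetry includes oximetry.
- That the lack of a heart-rate safety analysis is a defect in itself. A journal article may leave that to the full protocol or analysis plan.

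**Conclusion.** The point holds in limited form. Unequal detection is part of the design as described, and a common serious-event reporting rule does not equalise how non-serious events come to notice. Raw adverse-effect counts by arm would be confounded with surveillance, most likely in favour of the home arm. On the assumed rates above, equal true risks would appear as a ratio between 0.78 and 0.33, and the home arm would record fewer events with probability 0.50 to 0.94 over true risks of 10% to 30%. Those figures illustrate scale; they are not estimates for this trial. The effect is on the safety conclusion only. The efficacy comparisons and the sample size are untouched.

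**What to change.** In Sections 2.3 and 2.6:

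1. Base any between-arm comparison of adverse effects on serious adverse events and on one short set of adverse-effect questions, identical in both arms. Ask them at contacts that both arms already have: the end of the first month and the post-programme test. Record the answers as given by child and family, without adding to them from hospital session notes.
2. Report events found only through telemetry, pre-session vital signs or staff observation separately for the hospital arm, outside that comparison. State that their absence at home is not evidence of safety.
3. Heart rate above the prescribed range may be described within each arm if the data are stored. It should not be treated as equally ascertained: the devices differ, the hospital arm adds continuous exercise while the home arm does intervals only, and the article does not say that telemetry data are kept. Sessions stopped for symptoms have the same weakness, since staff judge in one arm and families in the other.

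The cost is a few added questions, with no extra visits, and a between-arm comparison that covers fewer event types. Recall over the roughly two months between the two contacts will lose some mild events, but the questioning is the same in both arms. No change to treatment, monitoring or sample size is implied.

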
### 2.3. Variable and Outcomes: Type and Measurement (Table 1)

The pediatric nurse will conduct a personal interview to collect the following data:
Demographic information such as name and surname, age and sex.Anthropometric measurements: height, weight, circumference of body, and composition.Relevant family history and associated comorbidity.Personal clinical information related to the condition: diagnoses (especially previous episodes of asthma or bronchospasm), surgical interventions, complications, functional alterations, medication, and timings.Sports habits during and outside school: type of sport practiced, and the amount of time spent per week.Rehabilitation diagnosis: a pediatric rehabilitation specialist will perform a comprehensive examination to identify any contraindications or biopsychosocial factors that may affect the implementation of the CRP.Quality of life questionnaires for children and adolescents with heart disease—PedsQL™ 4.0 Generic Core Scales and PedsQL™ Cardiac Module 3.0. Both questionnaires will be administered to the child, mother, and father separately.

**Table 1 jcm-14-00816-t001:** Evaluation flowchart.

Timeline	Evaluation Flowchart
First Visit	Ergo-spirometry Selection of patients. Provide written and verbal information to the patient and their family regarding the study and the procedures to be conducted. Obtaining informed consent.
Second Visit	Personal interview and measurement of vital signs. Quality of life questionnaires for children and adolescents with heart disease—PedsQL™4.0 Generic Core Scales and PedsQL™ Cardiac Module 3.0.

#### Outcomes (Table 2)

Assessment of respiratory function/spirometry: Spirometry is the study of choice in pulmonary function laboratories. The parameters it measures are the volume of air that the child breathes in or out in absolute value or related to time; and it is shown in the volume/time curve [33]. It also measures the flow expressed in curves with the flow/volume ratio. The mediations can be simple if slow breathing maneuvers not dependent on time are used or forced if maximum effort is requested in the shortest possible time, thus allowing the study of dynamic volumes and forced flows. The recording will be on a flow/volume curve. The most useful functional parameters obtained after spirometry are forced vital capacity (FVC), forced expiratory volume in the first second (FEV1), maximum expiratory flow (PEF), and the Tiffeneau index FEV1/FVC, FEF25%, FEF50%, FEF75%, FEF25–75%. [34]. The recording is called a spirogram.Classify, based on the results of spirometry, whether the child has restrictive [35], obstructive, or mixed ventilatory pattern:Restrictive pattern: defined as FVC and FEV1 < 80% of the predicted value, with FEV1/FVC > 80% or normal.Obstructive pattern: defined as FEV1/FVC ratio < 70%, FEV < 80%, and normal FVC.Mixed pattern: defined as FEV1 < 80%, FVC < 80%, and FEV1/FVC ratio that may be normal, increased, or decreased.Exercise capacity: Pediatric treadmill ergo-spirometry will be used. This test allows a non-invasive evaluation of the child’s functional capacity by calculating maximum oxygen consumption. It will be performed in our hospital on a treadmill following the Bruce protocol [36]. The Bruce protocol is a diagnostic tool increasingly used in the outpatient follow-up of these patients, in order to obtain an objective evaluation of the exercise capacity of children with CHDs and to know their real physical situation. It also has undeniable value for prescribing an individualized rehabilitation and physical exercise program. Exercise intensity is determined based on heart rate. This will be determined within the transition zone between the first ventilatory threshold (VT1) and the second ventilatory threshold (VT2). The values obtained in ergo-spirometry performed 6 months prior to the start of the intervention program will be used. Within two weeks after completing the cardio-respiratory physiotherapy program, a new test will be performed for comparative analysis.Quality of life: quality of life questionnaires for children and adolescents with heart disease—PedsQL^™^ 4.0 Generic Core Scales and PedsQL™ Cardiac Module 3.0.

**Table 2 jcm-14-00816-t002:** Evaluation protocol.

Measurements	Variable	Material and Methods	Unit of Measurements	Measurements	
				Pre	Post
Lack of adherence to the protocol	Absence	Absence in more than 20% of the sessions	Absence equivalent to missing 5 out of the 24 planned sessions		
Anthropometric data	Circumference of body	Flexible tape measure	cm	X	X
	Composition	Bioelectrical impedance	% body fat	X	X
	Height	Height meter	m/cm	X	X
	Weight	Bascule	kg	X	X
Ergo-spirometry	Oxygen consumption	Ergometer and Treadmill	VO_2_	X	X
Respiratory function	FEV1, FVC, FEV1/CVF, PEF, FEF25%, FEF50%, FEF75%, FEF25–75%	Spirometry	%	X	X
	Respiratory Pattern		Restrictive, Obstructive, and mixed	X	X
Perceived effort	Effort	Modified Borg scale	0–10	X	X

Note: m = meter; cm = centimeter; kg = kilogram; FEV1 = Forced expiratory volume in 1 s; FVC = Forced vital capacity; FEV1/CVF = Tiffeneau index; PEF = maximum expiratory flow; FEF = forced expiratory flow.

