#### 2.1.1. Inclusion Criteria

Individual case evaluation will determine eligibility for the Cardiac Rehabilitation Program (CRP). The pediatric cardiologist will assess each case and make decisions in conjunction with the patient’s family and the child or adolescent.

Participant selection will be based on the following criteria:Pediatric patients with a history of cardiac transplantation or CHDs who have undergone at least one interventional procedure or surgical intervention, at least 6 months before the start of the program in a state of clinical stability, hemodynamic stability, and ECG stability (ambulatory patient and does not require inotropic support or other therapies). They should have residual hemodynamic defects of sufficient severity that potentially restrict participation in physical activities, and their perception of fragility may be influenced by the social, family, school environment, or by the patient themselves.Children aged 8–17 years at the start of the study.Present a maximum oxygen consumption figure (peak VO_2_) below 80% of that predicted in ergo-spirometry performed prior to the start of the intervention program (in no case more than 6 months before the start).Patients who do not present contraindications for carrying out the program after evaluation in consultation with a pediatric cardiologist and a rehabilitation doctor.

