### 2.6. Data Analysis

The normality of the data distribution was analyzed with the test of Kolmogorov–Smirnov. For the descriptive analysis, the mean and standard deviation were used if the distribution of the variables was normal; otherwise, the median and interquartile range were calculated. The qualitative variables of the study will be defined by frequencies and percentages.

Student’s *t* test will be used to compare the intergroup means if the distribution of the variables is normal. The non-parametric Mann–Whitney U test will be applied if the normality of the data is not fulfilled. Levene’s test will be used to test the equality of variances between groups. Welch’s *t*-test will be used if the assumption is not met. Repeated measures t-test or the non-parametric Wilcoxon t-test will be applied for the comparison of intragroup means depending on the normality of the data. The Chi-Square test will be used to test the association between categorical variables.

A confidence level of 95% will be considered for the calculation of the confidence intervals and a significance level of 5% for the statistical tests. The statistical program IBM SPSS Statistics version 28.0.1 will be used to analyze the data.

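### The restrictive class lies wholly inside the mixed class, and normal spirometry has no class, so the categorical Respiratory Pattern outcome is not uniquely defined

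*Protocol article*

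**What the plan says.** The Outcomes section of the protocol article asks staff to determine "whether the child has restrictive [35], obstructive, or mixed ventilatory pattern". It then gives three rules:

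- "Restrictive pattern: defined as FVC and FEV1 < 80% of the predicted value, with FEV1/FVC > 80% or normal"
- "Obstructive pattern: defined as FEV1/FVC ratio < 70%, FEV < 80%, and normal FVC"
- "Mixed pattern: defined as FEV1 < 80%, FVC < 80%, and FEV1/FVC ratio that may be normal, increased, or decreased"

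Table 2 carries Respiratory Pattern as an outcome marked both Pre and Post, with the levels "Restrictive, Obstructive, and mixed". The same table records FEV1, FVC and their ratio, in %, at both times.

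The functional entry requirement in section 2.1.1 is "Present a maximum oxygen consumption figure (peak VO_2_) below 80% of that predicted in ergo-spirometry"; no spirometric limit is set. Section 2.2.1 expects that "most of the patients with CHDs have a restrictive ventilatory pattern (to be determined after ergo-spirometry analysis"), which leaves room for other patterns. The article gives no order in which the rules apply, no normal or residual class, and no cut-off for a normal FVC or a normal ratio.

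**The concern.** A categorical outcome needs levels that exclude one another and together cover every result. These three do neither. The restrictive and mixed rules set the same limits on the two volumes, and the mixed rule then leaves the ratio free. A child with low volumes and a preserved ratio satisfies both, so two careful assessors can label the same spirogram differently, and one child can change label between visits without any change in lung function.

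The list also has no place for a child whose spirometry is normal, at baseline or after the program. Restriction is the stated reason for the respiratory training, and respiratory function is part of the main objectives. The reported share of restrictive children, and any shift in pattern over 12 weeks, would depend on an unstated reading of the rules.

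**Working it through.** The plan gives no figure to reproduce. The check is one of logic.

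**Inputs (Outcomes section)**

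- Restrictive: FVC < 80, FEV1 < 80, and ratio > 80 or normal.
- Obstructive: ratio < 70, FEV < 80 (read as FEV1), FVC normal.
- Mixed: FEV1 < 80, FVC < 80, any ratio.

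**Assumptions**, because the article gives no cut-offs: normal FVC is 80% predicted or more; the lower limit of a normal ratio is tried at 70, 75, 80 and 85%.

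**Overlap.** Restrictive is the mixed condition with one further restriction, on the ratio. It is therefore a strict subset of mixed wherever normal is set. As a check, the rules were applied to a grid of 6 FEV1 values × 6 FVC values × 7 ratios = 252 combinations. Both volumes are low in 3 × 3 × 7 = 63 of them, and all 63 meet mixed.

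| Assumed lower limit of a normal ratio | Meets restrictive | Of these, also meets mixed | Mixed only |
|---|---|---|---|
| 70% | 45 | 45 | 18 |
| 75% | 36 | 36 | 27 |
| 80% | 27 | 27 | 36 |
| 85% | 18 | 18 | 45 |

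No combination is restrictive only. If mixed is read first, the restrictive count is 0. If restrictive is read first, it is every combination with low volumes and a non-reduced ratio. Even then, it moves from 45 to 18 with the undefined meaning of a normal ratio.

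**Gaps.** Obstructive takes 3 × 3 × 2 = 18 combinations and overlaps neither other class. Combinations with no class: 252 − 63 − 18 = 171, at every assumed cut-off. They are:

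- FEV1 ≥ 80 and FVC ≥ 80, which includes normal spirometry: 3 × 3 × 7 = 63;
- FVC < 80 with FEV1 ≥ 80: 3 × 3 × 7 = 63;
- FEV1 < 80 with FVC ≥ 80 and ratio ≥ 70: 3 × 3 × 5 = 45.

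The sum is 63 + 63 + 45 = 171. These counts show which regions are uncovered. They are not proportions of patients, and not every grid point need occur in a real child.

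**Can the gaps arise?** Entry rests on peak VO2, so a child with normal spirometry can be enrolled. A child who starts with low volumes and recovers has no level to move to.

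**The case against.** The strongest reply is that little depends on this variable. Pattern is not among the measures named in the Abstract, nor is it named in the objectives. It decides neither entry nor treatment: both arms receive respiratory training, and section 2.2.1 expects children with obstructive or mixed patterns to benefit as well. The sample size rests on a difference in means. FEV1, FVC and the ratio are recorded at both visits, so any class can be re-derived and recovery is visible in the continuous values. All of this stands, and it limits the point to one categorical variable. It does not remove the conflict, because the article states the definitions in full and they disagree with one another.

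It could also be said that asking whether a child has one of the three patterns allows the answer none. That would cover normal spirometry in the text, but Table 2 offers no such level, and the restrictive–mixed overlap would remain.

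A reader might infer several stronger points that the article does not support:

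- **That the whole outcome is unclassifiable.** Obstructive cases, and low volumes with a reduced ratio, each receive a single label.
- **That the restrictive share could reach every child with low FVC and FEV1.** Those with a reduced ratio are mixed on any reading.
- **That an unblinded team could relabel children between visits.** The article does not say who classifies or whether they are blinded.
- **That the planned test is invalid for pre–post change.** Section 2.6 says "The Chi-Square test will be used to test the association between categorical variables" and does not assign that test to paired data. Paired categorical methods and small-cell alternatives are commonly left to an analysis plan, which is not shown here.
- **That expected counts will be too small.** In an arm of 26, an expected count below 5 needs a class share below 5/26 = 19%, and the article gives no class shares.

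**Conclusion.** The point holds for the categorical Respiratory Pattern variable. All children who meet the restrictive rule also meet the mixed rule, whatever cut-off is taken for a normal ratio. Their reported share can lie anywhere from zero to all children with low FVC, low FEV1 and a non-reduced ratio. Three regions of spirometric results, among them normal spirometry, have no level in Table 2.

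The overlap follows from the wording alone. The exact edges of the gaps assume that normal FVC means 80% predicted or more. How many children are affected cannot be stated, because the article gives no distribution of patterns.

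The continuous spirometry outcomes, peak VO2, the comparison of arms on them and the sample size are untouched. This is a defect in one listed outcome that should be put right before analysis; it does not threaten the trial's main comparisons.

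**What to change.** Before analysis, reword the three definitions in the Outcomes section so that each result falls in exactly one class:

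1. Separate mixed from restrictive by whether FEV1/FVC is reduced. The investigators should choose and state the cut-offs for a reduced ratio and for a normal FVC.
2. Add a normal level and an unclassified level, in both the Outcomes text and Table 2.
3. Derive the class by that written rule from the recorded FEV1, FVC and FEV1/FVC, in the same way at the pre and post visits.

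The cost is a revision of the definitions and two more levels in one table row. No new measurement, visit or change in sample size is needed, and because the class is computed from values already recorded, it can be applied to children already assessed. The choice of test for the revised variable can be left to the analysis plan.
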